## Abstract

**Background:**

Globally, bronchiectasis (BE) unrelated to cystic fibrosis (CF) is recognized as a major cause of respiratory morbidity, mortality, and healthcare utilization. Children with BE regularly experience exacerbations of their condition resulting in frequent hospitalizations and decreased health-related quality of life (HR-QoL). Guidelines for the treatment and management of BE call for regular exercise as a means of improving aerobic fitness and HR-QoL. Moreover, research in adults with BE has shown that exercise can reduce the frequency of exacerbations, a potent predictor of future lung function decline and respiratory morbidity. Yet, to date, the health benefits resulting from therapeutic exercise have not been investigated in children with BE. The BREATH, Bronchiectasis - Exercise as Therapy, trial will test the efficacy of a novel 8-week, play-based therapeutic exercise program to reduce the frequency of acute exacerbations over 12 months in children with BE (aged ≥ 4 and < 13 years). Secondary aims are to determine the cost-effectiveness of the intervention and assess the program’s impact on aerobic fitness, fundamental movement skill (FMS) proficiency, habitual physical activity, HR-QoL, and lung function.

**Methods:**

This multi-center, observer-blinded, parallel-group (1:1 allocation), randomized controlled trial (RCT) will be conducted at three sites. One hundred and seventy-four children ≥ 4 and < 13 years of age with BE will be randomized to a developmentally appropriate, play-based therapeutic exercise program (eight, 60-min weekly sessions, supplemented by a home-based program) or usual care. After completing the baseline assessments, the number of exacerbations and secondary outcomes will be assessed immediately post-intervention, after 6 months of follow-up, and after 12 months of follow-up. Monthly, parental contact and medical review will document acute respiratory exacerbations and parameters for cost-effectiveness outcomes.

**Discussion:**

The BREATH trial is the first fully powered RCT to test the effects of a therapeutic exercise on exacerbation frequency, fitness, movement competence, and HR-QoL in children with bronchiectasis. By implementing a developmentally appropriate, play-based exercise program tailored to the individual needs of children with bronchiectasis, the results have the potential for a major paradigm shift in the way in which therapeutic exercise is prescribed and implemented in children with chronic respiratory conditions. The exercise program can be readily translated. It does not require expensive equipment and can be delivered in a variety of settings, including the participant’s home. The program has strong potential for translation to other pediatric patient groups with similar needs for exercise therapy, including those with obesity, childhood cancers, and neurological conditions such as cerebral palsy.

**Trial registration:**

Australian and New Zealand Clinical Trials Register (ANZCTR) ACTRN12619001008112

## Administrative information

Note: The numbers in curly brackets in this protocol refer to SPIRIT checklist item numbers. The order of the items has been modified to group similar items (see http://www.equator-network.org/reporting-guidelines/spirit-2727-statement-defining-standard-protocol-items-for clinical-trials/).

## Introduction

### Background and rationale {6a}

Bronchiectasis (BE) unrelated to cystic fibrosis (CF) is a major cause of respiratory morbidity and a significant contributor to health care utilization in children and adolescents globally [1–3]. It is the end point of the chronic suppurative lung disease (CSLD) continuum and is described as abnormal irreversible dilatation of the airways and associated with airway infection and inflammation [4, 5]. Children with BE regularly experience exacerbations of their condition (increased wetness and severity of cough, breathlessness, chest pain, and/or wheeze) resulting in frequent hospitalizations and decreased health-related quality of life (HR-QoL) [2, 6]. Prevalence data in children are scarce; however, a recent review of the epidemiology of CLSD estimated the prevalence of BE to range from 0.2 to 15 cases per 100,000 [7]. BE is particularly prevalent among socially disadvantaged populations, such as indigenous communities of Australia, New Zealand, Alaska, and Canada [7, 8]. A study of Central Australian Aboriginal children reported the prevalence as high as one in every 68 children [9].

The treatment goals of multi-disciplinary management are to prevent airway damage and optimize quality of life and minimize exacerbations [4]. Current clinical treatment guidelines recommend general exercise to improve aerobic fitness and HR-QoL [9]. However, the health impacts associated with therapeutic exercise in children with BE are not well understood [9, 10]. A recent meta-analysis of the effects of exercise training on physical and psychosocial health in children with chronic respiratory disease identified no published studies investigating the impact of therapeutic exercise in this population [11]. Therapeutic exercise may benefit children with BE by reducing the frequency and severity of acute exacerbations—an independent predictor of a long-term decline in lung function [6]. A randomized controlled trial (RCT) evaluating the effects of an 8-week exercise program in adults with BE reported significant reductions in the number of acute exacerbations over a 12-month period [12]. Moreover, therapeutic exercise programs may also reduce the risk of disabling secondary conditions such as obesity, depression, and anxiety [13].

It is known that children with BE are not sufficiently active to obtain the health benefits associated with regular physical activity (PA). Using an accelerometer to objectively measure daily physical activity, Joschtel and colleagues [14] found children with BE to have low levels of moderate-to-vigorous intensity physical activity (MVPA). Expressed as a percentage of the waking hours, children with BE were sedentary for 57.5% of the time, in light-intensity PA 35.8% of the time, and in MVPA just 6.7% of the time. Indeed, only two children (5.6%) achieved the recommended 60 min of daily MVPA described in the Australian 24-Hour Movement Guidelines for Children and Young People. In contrast, 42% of healthy children in the normative comparison group achieved the guideline. On average, children with BE accumulated 8229 steps/day, well below the recommended 12,000 steps/day. In comparison, daily step counts in healthy children ranged from 11,500 to 14,500 steps/day.

Fundamental movement skill (FMS) proficiency is an important determinant of children’s current and future physical activity status and a significant contributor to individual health and well-being [15]. The development of FMSs early in life is critical to establishing the more complex movement patterns required for participation in all types of play, games, physical activities, and sports [15–17]. Children who are proficient in FMSs are more likely to participate in and enjoy physical activity, achieve higher levels of aerobic fitness, exhibit higher levels of perceived competence and self-esteem, and are less likely to be overweight or obese [15–17]. It has been shown that children with BE exhibit significant delays in their FMS development, thus compromising their ability, confidence, and motivation to participate in PA [18]. In a study of 46 children with BE, only nine (19.6%) achieved their age equivalency for locomotor skills, while just four (8.7%) achieved their age equivalency for object control skills. Fewer than 5% of children demonstrated mastery in the run, gallop, hop, and leap, while fewer than 10% demonstrated mastery for the two-handed strike, overarm throw, and underarm throw. Importantly, children achieving their age equivalency for locomotor or object control skills exhibited higher levels of MVPA, perceived competence, and HR-QoL than children with developmental delays in FMSs.

To address the concerns that children with BE are insufficiently active for health benefits and that developmental delays in fundamental movement skill proficiency are a root cause, we have developed a novel, play-based therapeutic exercise program specifically designed to improve FMS proficiency and aerobic fitness in children with BE. In a pilot RCT involving 21 children with BE, the program significantly improved FMS proficiency, with a 21% increase in locomotion skills and a 31% increase in object control. The effect sizes associated with these improvements were, by convention, large (Cohen’s *d* ≥ 1.2). The program also had a moderate positive effect on aerobic fitness (Cohen’s *d* = 0.5) [14, 19]. We now propose to expand this program to a large multi-center RCT to evaluate the efficacy of our exercise program in reducing the frequency of acute exacerbations of BE. Exacerbation frequency is the only known risk factor for lung function decline in children with BE [20]. Reducing the frequency of exacerbations during childhood through therapeutic exercise may be an important clinical management strategy for preventing a future decline in lung function and respiratory morbidity later in life.

### Objectives {7}

This multi-center RCT is designed to answer the primary research question: does therapeutic exercise decrease the frequency of exacerbations in children with BE? Therefore, the primary objective is to test the efficacy of a novel 8-week, play-based therapeutic exercise program to reduce the incidence of acute exacerbations over 12 months in children with BE aged ≥ 4 and < 13 years. The primary hypothesis is that the proportion of children with no exacerbations at 12 months will be significantly higher in participants receiving an exercise program than in participants in the wait-list control condition.

The secondary objectives are to (1) conduct an economic evaluation of the program and (2) evaluate the effects of the program on FMS proficiency, objectively measured moderate-to-vigorous physical activity (MVPA), cardiorespiratory function (CRF), perceived movement competence, health-related quality of life (HR-QoL), and lung function (FEV1). Our secondary hypothesis is that the program will be cost-effective and efficacious in improving FMS proficiency, daily MVPA, CRF, perceived movement competence, HR-QoL, and lung function.

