### Trial design {8}

The BREATH trial is designed as a randomized, controlled, multi-center, observer-blinded, parallel-group (1:1 allocation), superiority trial. Following informed consent/assent, enrolled children will complete baseline assessments (T1). Participants will then be randomized to either the therapeutic exercise program or wait-list control condition. The number of exacerbations and secondary outcomes will be assessed immediately post-intervention at 9 weeks (T2), after 6-months of follow-up (T3), and after 12 months of follow-up (T4).

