#### Primary outcome

Pulmonary exacerbation will be defined as treatment with antibiotics for any of the following: increased wet cough, dyspnea, increased sputum volume or color intensity, new chest examination or radiographic findings, deterioration in FEV1 percentage by more than 10%, or hemoptysis [22]. Wet cough must be present. Monthly, parental contact and medical review at each assessment time point will document acute respiratory exacerbations.

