## Statistical methods

### Statistical methods for primary and secondary outcomes {20a}

The statistical analyses will follow standard principles for RCTs using two group comparisons including all participants on an intention-to-treat basis. For the primary objective, a binary regression model with a suitably chosen link function (e.g., logistic) will be used where the target variable is whether or not an exacerbation occurred over the 12-month study period for each subject. The main covariate of interest is the treatment group (exercise vs. wait-list control). Other covariates potentially influencing the target variable such as age and sex will be considered. Therefore, the statistically determined treatment effect will be appropriately adjusted for unbalanced data with respect to the other important covariates retained in the regression model. Between-group differences in secondary outcomes—aerobic fitness, habitual PA, perceived competence, HR-QoL (PedsQL), and lung function (FEV1)—will be tested immediately post-intervention, at 6 months follow-up, and at 12 months follow-up using linear regression with treatment group (exercise vs. wait-list control) as the main effect and baseline measures of the respective outcome, along with other potential confounders (e.g., age, sex), as covariates.

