### Methods for additional analyses {20b}

No other additional analyses are planned.

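### The primary question is about exacerbation frequency and counts are recorded, but only any-versus-none is analysed; the list of secondary outcomes to be tested also omits FMS proficiency

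*Protocol article*

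**What the plan says.** Under Objectives {7} of the protocol article, one paragraph describes the primary target in three ways. The research question is "does therapeutic exercise decrease the frequency of exacerbations in children with BE". The objective is "to reduce the incidence of acute exacerbations over 12 months in children with BE aged" 4 to under 13 years. The hypothesis is binary: "The primary hypothesis is that the proportion of children with no exacerbations at 12 months will be significantly higher" with exercise than on the wait list.

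On data collection, Trial design {8} states: "The number of exacerbations and secondary outcomes will be assessed immediately post-intervention at 9 weeks (T2"), and again after 6 and 12 months of follow-up. The Primary outcome section adds: "Monthly, parental contact and medical review at each assessment time point will document acute respiratory exacerbations".

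On analysis, Statistical methods {20a} specifies a binary regression in which "the target variable is whether or not an exacerbation occurred over the 12-month study period for each subject". No model for the number or rate of exacerbations is given. Methods for additional analyses {20b} reads: "No other additional analyses are planned".

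For the secondary outcomes, {20a} specifies baseline-adjusted linear regression and lists what will be tested: "aerobic fitness, habitual PA, perceived competence, HR-QoL (PedsQL), and lung function (FEV1"). FMS proficiency is not in that list. It is the first effect outcome named in secondary objective (2), it is in the secondary hypothesis, it is the first secondary outcome in the Fig. 1 legend, and it has its own measure, the TGMD-2.

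**The concern.** Frequency and any-versus-none are different quantities. A child who would have had four exacerbations and has one instead has clearly benefited, but the binary variable scores that child the same as one with no change. The Sample size section expects 80% of controls to have at least one exacerbation, so for most children the benefit could lie in how many they have, and that part of the recorded data enters no stated analysis.

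This matters for what the trial may say at the end. The abstract presents it as fully powered for exacerbation frequency, and the background justifies it by the link between exacerbation frequency and lung function decline. What is powered and analysed is a proportion. A frequency result reported without a pre-specified model would be open to the charge of being post hoc.

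The FMS gap is a separate and simpler matter. The background describes the programme as built to improve movement skills, yet the itemised list of tests does not include them.

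**Working it through.** **Inputs from the Sample size section.** Exacerbation-free at 12 months: 20% (control) v 40% (exercise); two-sided alpha 0.05; 79 per group; 80% power.

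**Step 1: the plan's own figure.** Unpooled two-proportion formula: n = (1.960 + 0.842)² × (0.2×0.8 + 0.4×0.6) / 0.2² = 78.49, so 79 per group. This reproduces the stated size. At n = 79 the power is 80.3% by the unpooled formula and 78.9% by the pooled one. The sample size fits the binary endpoint.

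**Step 2: turning the binary assumption into rates.** The article gives neither a mean count nor a dispersion, so the dispersion k is assumed at 0 (Poisson), 0.5 and 1. The mean μ is set to give the stated proportion with no event:
- Poisson: P(0) = exp(−μ), so μ = −ln P(0).
- Negative binomial: P(0) = (1 + kμ)^(−1/k), so μ = (P(0)^(−k) − 1)/k.

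For P(0) = 0.20 the control means are 1.61 (k = 0), 2.47 (k = 0.5) and 4.00 (k = 1) per year. For P(0) = 0.40 the means are 0.92, 1.16 and 1.50. The planned 20% v 40% therefore implies rate ratios of 0.57, 0.47 and 0.38.

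**Step 3: power formulas.**
- Count model: SE(log RR) = √{[(1/μ0 + k) + (1/μ1 + k)]/79}; power = Φ(|log RR|/SE − 1.960).
- Binary test (pooled): power = Φ{[|p1 − p0|√79 − 1.960√(2p̄(1 − p̄))] / √(p0(1 − p0) + p1(1 − p1))}.

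Worked case, k = 0 at 20% v 40%: SE = √[(1/1.609 + 1/0.916)/79] = 0.147; |log RR| = 0.563; 0.563/0.147 − 1.960 ≈ 1.87; power 97%.

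Worked case, k = 0 with an assumed rate ratio of 0.70: μ1 = 1.127; SE = √[(1/1.609 + 1/1.127)/79] = 0.138; 0.357/0.138 − 1.960 ≈ 0.62; power 73%. The exacerbation-free share rises only to exp(−1.127) = 32%, and the binary power is 43%.

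**Step 4: results with 79 per arm.**

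| Scenario | k | Control mean per year | Rate ratio | Exacerbation-free, exercise | Binary power | Count power |
|---|---|---|---|---|---|---|
| Planned 20% v 40% | 0 | 1.61 | 0.57 | 40% | 79–80% | 97% |
| Planned 20% v 40% | 0.5 | 2.47 | 0.47 | 40% | 79–80% | 99% |
| Planned 20% v 40% | 1 | 4.00 | 0.38 | 40% | 79–80% | >99% |
| Assumed 30% rate cut | 0 | 1.61 | 0.70 | 32% | 43% | 73% |
| Assumed 30% rate cut | 0.5 | 2.47 | 0.70 | 29% | 25% | 61% |
| Assumed 30% rate cut | 1 | 4.00 | 0.70 | 26% | 15% | 50% |

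**Step 5: FMS, by comparison of sections.** Secondary objective (2) names FMS proficiency, MVPA, cardiorespiratory function, perceived movement competence, HR-QoL and FEV1. The list in {20a} has a counterpart for every one of these except FMS proficiency. The outcomes section and the Fig. 1 legend both treat FMS as a secondary outcome.

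**The case against.** The binary endpoint is deliberate and consistent. It is the explicit primary hypothesis, and the economic evaluation, the Fig. 1 legend, the sample size and the model all use it. The proportion with at least one event over 12 months is a cumulative incidence, so the objective's word incidence can be read as matching the analysis. All of this stands. A reader might infer that the frequency objective goes unanswered, or that the primary endpoint is wrong; the article supports neither. The hypothesis will be tested, and the result bears on frequency.

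The statement under {20b} concerns additional analyses. It does not withdraw an outcome named elsewhere, and the method in {20a} applies to TGMD-2 scores as it stands. A reader might infer that the trial cannot test its FMS hypothesis; what the article shows is a list that disagrees with other sections.

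A supportive count model could be left to a statistical analysis plan. That has weight, but the article itself poses the question as frequency and says that it counts events, then states an analysis of something else and adds that nothing further is planned. The mismatch is in the printed text.

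The power figures rest on assumptions. Fixing 20% event-free with more dispersion forces control means of 2.5 or 4.0 per year, and power of 99% or more at 20% v 40% then requires a rate cut of 53% or 62%. Every scenario also assumes the same proportional effect throughout. The figures illustrate the direction and rough scale of the loss; they do not measure it.

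**Conclusion.** The point holds in a limited form. The frequency question is only partly answered, because reductions among children who still have at least one exacerbation enter no stated analysis although the counts are recorded. FMS proficiency is missing from the list of outcomes to be tested, which contradicts the objectives, the outcome section and the Fig. 1 legend.

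The possible loss is large under every dispersion tried: count-model power exceeds binary power by 30 to 36 percentage points at an assumed rate ratio of 0.70 (73 − 43, 61 − 25, 50 − 15), and by about 17 points or more at the planned 20% v 40%. The 30% rate reduction, the dispersion and the mean counts are assumptions. A reader might also infer that adding a count model would strengthen the primary test. It would not: the power of that test stays as it is, and its sample size is correctly derived.

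**What to change.** 1. Keep the powered binary primary analysis, and word the primary question and objective as the proportion of children exacerbation-free over 12 months.
2. Pre-specify as a key secondary a negative binomial regression of the number of exacerbations from randomisation to T4, with log follow-up time as offset and arm and site as terms. Add the prior-year exacerbation count only if it is captured at baseline; the article requires at least one prior exacerbation for entry but does not say that the number is recorded. Base any statement about frequency on this rate ratio.
3. Add the TGMD-2 locomotor and object-control scores to the list of baseline-adjusted regressions in {20a}, and bring {20b} into line.

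The cost is some rewording and one more model on events already being documented. The small downside is that a count needs a rule for when a further antibiotic course is a new exacerbation, and the article's outcome definition gives none. These changes should be fixed before anyone sees outcome data by arm.

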### Trial design {8}

The BREATH trial is designed as a randomized, controlled, multi-center, observer-blinded, parallel-group (1:1 allocation), superiority trial. Following informed consent/assent, enrolled children will complete baseline assessments (T1). Participants will then be randomized to either the therapeutic exercise program or wait-list control condition. The number of exacerbations and secondary outcomes will be assessed immediately post-intervention at 9 weeks (T2), after 6-months of follow-up (T3), and after 12 months of follow-up (T4).

## Methods: participants, interventions, and outcomes

### Study setting {9}

The RCT will be conducted at the Queensland Children’s Hospital (QCH), Gold Cold University Hospital (GCUH), and Royal Darwin Hospital (RDH) in Australia. QCH is a metropolitan tertiary level hospital providing specialized services to children living in Queensland and northern New South Wales. The QCH has a dedicated Respiratory and Sleep Medicine Department with approximately 15 senior medical officers. GCUH is a tertiary-level facility that includes a pediatric respiratory service with two pediatric respiratory physicians. RDH is a tertiary level hospital and the largest in the Northern Territory that includes a pediatric respiratory service with a respiratory consultant.

### Eligibility criteria {10}

To be eligible for enrollment, participants must be ≥ 4 and < 13 years of age, have a confirmed diagnosis of non-CF BE (by high-resolution chest tomography (HRCT)), or if > 5 years since the last scan, under the regular care of a pediatric pulmonologist; experienced at least one acute pulmonary exacerbation in the past twelve months; and be medically able to participate in the exercise, have their parent provide informed consent, and not be planning to leave the study catchment area in the 12 months following enrollment. Participants will be excluded if they are unstable medically (as advised by the treating pulmonologist), have insufficient cooperation and/or cognitive understanding to perform tasks, have a recent musculoskeletal injury (e.g., muscle strain, sprains, fractures), have an underlying chronic illness other than BE (e.g., CF, neurological or cardiac disorders), are participating in a clinical trial of another investigational drug/devise or interventional therapy, and are unable to attend sessions or return for follow-up assessments.

